### Assessment of pain, function, general quality of life and clinical markers

Physical functional will be measured using the Timed Up and Go assessment [25]. Briefly, this test involves the client standing up from an armless chair and walking around a cone placed 2.44 m in front of the chair, returning to the chair and sitting down. It is a reliable and valid measure of physical function that is used widely in clinical practice [26].Quality of life will be evaluated using the SF-12. This survey includes 12 items which capture information on two subscales describing physical well-being (the physical component summary) and mental well-being (the mental component summary). It is validated and has been widely used to measure quality of life in a range of populations [27–29].The visual analogue scale is a unidimensional valid measure of pain intensity [30], which has been shown to be sensitive to clinical change in people with arthritis. The Oxford Hip and Knee Function scales are clinically useful patient self-report tools, originally designed to be administered to determine the efficacy of joint replacement [31]. They contain 12 questions related to the impact of their condition on daily functioning over the previous 4 weeks. The hip assessment tool is valid, reliable and responsive to change [32]. The Oxford Knee Scale has good internal validity [31].Three indicators of body composition (body mass index, waist circumference and percent body fat) will be measured. These measures are simple and easy to attain and have been widely used as indicators of cardiovascular disease [33] and mortality risk [34] in large-scale population studies. Body mass index will be calculated from height and body weight. Waist circumference will be measured at the narrowest point between the base of the ribcage and the iliac crest as per standard methods. Body fat percentage will be assessed with bio-impedance analysis scales (Tanita BC-1000; Tanita Corp; Tokyo, Japan), which have previously been shown to be a reliable and reproducible method for determining body composition [35].Brachial blood pressure will be measured with an aneroid sphygmomanometer by an experienced practitioner using standardised techniques after 5 minutes of seated rest.Blood measures of metabolic health [blood glucose and glycosylated haemoglobin (HbA1c)] will be measured from finger-prick blood samples using point of care analysers. Random blood glucose will be measured using a Hemocue Point of Care device (Hemocue Glucose 201; Hemocue AB; Angelholm, Sweden), a reliable and valid device for measuring blood glucose [36]. HbA1c will be measured with a DCA Vantage point of care analyser (Siemens Healthcare, Tarrytown, NY). The DCA Vantage analyser has previously been demonstrated to be a reliable and valid method for determining HbA1c [37].

### Assessment of psychological HAPA-based constructs

*Regular exercise* will be assessed using a multi-item scale. ‘Think about the past week. In general, how often did you do regular exercise?’ Responses are rated from 1 (never) to 4 (very often). ‘Think about the past week. In general, to what extent did you do regular exercise?’ Responses are rated from 1 (never) to 4 (a large extent). In addition, an open format item ‘Think about the entire past week and count, how many days you did exercise (e.g., if you exercised for at least 20 minutes at a time every day then the response is 7)?’*Habit strength* is assessed using the four-item Self-Report Behavioural Automaticity Index [38]. A sample item is ‘Do you agree that doing regular exercise is something… I do automatically?’ Responses are rated from 1 (strongly disagree) to 7 (strongly agree).*Intention* is assessed with three items. A sample item is ‘In regards to doing regular exercise over the next week, do you agree that… I intend to exercise?’ Responses are rated from 1 (strongly disagree) to 7 (strongly agree).*Attitude* is assessed with three items. A sample item is ‘Doing regular exercise over the next week would be… unpleasant.’ Responses are rated on semantic differential scales from unpleasant to pleasant, bad to good, or harmful to beneficial.*Social influence* is assessed with four items. A sample item is ‘In regards to doing regular exercise over the next week, do you agree that… People give me support to ensure I regular exercise?’ Responses are rated from 1 (strongly disagree) to 7 (strongly agree).*Perceived Behavioural Control* is assessed with four items. A sample item is ‘In regards to doing regular exercise over the next week, do you agree that… I have complete control over whether I do regular exercise?’ Responses were rated from 1 (strongly disagree) to 7 (strongly agree).*Barrier self-efficacy* is assessed with five items. A sample item is ‘I am confident I can do regular exercise over the next week… even when I am in pain.’ Responses are rated from 1 (not at all confident) to 7 (definitely confident).*Action planning* is assessed with four items. A sample item is ‘In regards to doing regular exercise over the next week, do you agree that I have made a plan regarding… When to regularly exercise?’ Responses are rated from 1 (not at all true) to 7 (definitely true).*Action control* is assessed with three items. A sample item is ‘During the last week… I have often had my regular exercise intentions on my mind?’ Responses are rated from 1 (not at all true) to 7 (definitely true).

### Programme adherence

Participants randomised to the exercise intervention will be allocated to exercise classes based on their starting date and availability. Adherence is categorised as follows: participation in 75% or more of the supervised sessions is excellent, participation in 50–74% of sessions is good, participation in 25–49% of sessions is moderate and participation in less than 25% of the sessions is poor. Adherence to exercise during the exercise intervention will be measured via attendance sheets at group training sessions. After the exercise intervention, participation in the prescribed home exercise will be evaluated via self-report (questionnaire) collected at test 2 and test 3.

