**Method/design:**

The exercise and behaviour change counselling (ENHANCE) trial is a two-arm assessor-blind randomised controlled trial to assess the effectiveness of a 12-week exercise intervention designed to improve long-term physical activity and functional abilities for people awaiting arthroplasty. Participants on the waiting list for hip and knee arthroplasty are recruited from one clinical site in Australia. After collection of baseline data, participants are randomised to either an intervention or control group. The control group receive usual care, as recommended by evidence-based guidelines. The intervention group receive an individualised programme of exercises and counselling sessions. The 12-week exercise programme integrates multiple elements, including up to five in-person counselling sessions, supported by written materials. Participants are encouraged to seek social support among their friends and self-monitor their physical activity. The primary outcome is physical activity (daily step count and percentage of day spent in sedentary activities). Secondary outcomes include pain ratings, physical function, psychosocial factors and changes in clinical markers linked with potential common chronic diseases (diabetes and cardiovascular disease). All outcomes are assessed at baseline and 26 weeks later and again at 26 weeks post-surgery.

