#### Exercise programme

The exercise programme will be individualised based on the assessment at entry by an AEP who has experience in the delivery of exercise to people with chronic health conditions. The intensity and progression of exercises will be determined on an as-needs basis and will include both the class-based programme and home-based exercises. The required elements of the exercise programme will be based on clinical evidence for hip and knee OA [23] and are outlined in Table 1. The dose will be determined by the supervising AEP in negotiation with each participant’s preferences and clinical status.

**Table 1 Tab1:** Exercise components

Exercise component	Supervised (twice weekly)	Unsupervised (home)
Aerobic component	40–60% HR max, 12–14 repetitions; walking, cycling or arm ergometry	Low to moderate intensity (40–60% HR max, 12–14 repetitions); a home programme aiming to accumulate 20–30 min a day for 2–5 days a week will be progressively introduced where safe and practical
Flexibility: static stretching	Building to 3–5 stretches of up to 30 s duration	Initially, once daily at home to comfortable end of range (up to 15 s holds)
Strengthening isometric exercises	40% MVC with up to 10 holds for up to 6 s	Where safe and practical, this will be expanded to the home exercise programme and repeated daily
Strengthening isotonic exercises with TheraBands	40% MVC up to 15 repetitions	Will commence at low levels (40% MVC with between 10 and 15 repetitions) and progress when possible to higher loads and fewer repetitions to stimulate strength gains; once weekly

*HR max* maximum heart rate, *MVC* maximal voluntary contraction

The AEP will regularly review participants’ original or amended goals, participation in their home exercise programme since the previous class, barriers experienced, motivation for exercise, recent symptoms and pain status. Attendance and adverse events will be documented.

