### Usual care

Participants in the control group receive a generic information brochure at their baseline assessment point, *Arthritis (osteoarthritis) and exercise*, produced by Exercise is Medicine Australia [24]. Otherwise, participants allocated to usual care receive their concomitant care while they are on the surgical waiting list, attending for ENHANCE assessments at 6 months after baseline and at 6 months after their surgery.

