### Randomisation

After completing all baseline data collection measures, participants are randomised to either the intervention group or the control group. Participants in the intervention group receive evidence-based physical activity guidelines supervised by an AEP for the 12 weeks. In addition, those in the intervention group receive an instructor-developed exercise booklet, along with innovative counselling classes five times directly after their exercise session. Participants in the control group will receive an information sheet with general advice on the benefits of physical activity for adults with OA. Participants in either group may receive relevant concomitant care and interventions.

The randomisation schedule has been prepared by a researcher independent of the research project using a computer-generated random number table. To conceal randomisation, the independent researcher has prepared consecutively numbered, sealed, opaque envelopes, which are kept in a locked location. As ENHANCE is an exercise intervention, blinding of the participants and the researchers who conduct the exercise sessions is not possible. Outcome assessors will not be involved in the delivery of the intervention and will be blinded to group allocations.

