### Assessment

All staff at the trial site have been trained in the study protocol and the procedures for collecting informed consent and assessment data. A data collection training manual has been developed to guide research staff in the administration of the informed consent and data collection procedures. Assessments are completed in person at baseline, at 26 weeks and at 26 weeks post-surgery (Fig. 1). Once the data have been entered into the local database, they will be transferred to the data manager for the trial, who will compare the hard copies with the database to check accuracy. The data manager will check all the primary outcome variables and a randomly chosen 20% of the other variables. If there are any errors in the primary outcomes, or more than 1% errors for other variables, all data will be checked. The database will not include the assigned treatments. These will be recorded in a separate database, so that the statistician analysing the data will remain blind to treatment allocation.

Potential participants complete a brief screening by telephone conducted by the research nurse. During the screen, an in-person baseline assessment is scheduled for eligible participants. Informed consent is obtained before the assessment. All questionnaires are administered by an interviewer. All baseline and follow-up assessments will be conducted at the intervention site.

All assessment sessions (baseline [time 1], week 26 [time 2] and 26 weeks post-surgery [time 3]) will include a measurement of the primary and secondary outcomes. An ENHANCE questionnaire on data related to the HAPA constructs and a range of dimensions related to health outcomes will also be administered (see Table 2). The baseline assessment will collect additional demographic information related to health, medical history and general health status.

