### Primary outcome measure

The primary outcome measure is daily physical activity (daily step count and percentage of day spent in sedentary activities). Participants will wear an activity monitor (activePAL™) for seven consecutive days. Data from the device will be recorded and uploaded to a computer. These data will be averaged over the 7 days of activity to calculate a daily step count. The percentage of the day spent in sedentary activities will also be recorded. This measure will be taken upon entry to the study (test 1), and at approximately 6 months (test 2), and then at 6 months after surgery (test 3).

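### As written, the interviewer can learn allocation from the home-exercise adherence questionnaire at tests 2 and 3, contrary to the stated assessor blinding

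*Protocol article*

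**What the plan says.** The Abstract states that ENHANCE "is a two-arm assessor-blind randomised controlled trial". Under Randomisation, participants and the staff who run the exercise sessions are acknowledged to be unblinded, and the safeguard is then given: "Outcome assessors will not be involved in the delivery of the intervention and will be blinded to group allocations".

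Three other sections bear on whether that can be kept:

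- **Assessment.** "All questionnaires are administered by an interviewer". No questionnaire is exempted. The same section says that all sessions, tests 2 and 3 included, "will include a measurement of the primary and secondary outcomes".
- **Programme adherence.** Class attendance is taken from attendance sheets. After the programme, "participation in the prescribed home exercise will be evaluated via self-report (questionnaire) collected at test 2 and test 3".
- **Exercise programme and Usual care.** The intervention arm's exercise plan "will include both the class-based programme and home-based exercises", with the home elements set out in Table 1. For the other arm: "Participants in the control group receive a generic information brochure at their baseline assessment point". Otherwise controls continue with their concomitant care, and no home prescription is described for them.

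**The concern.** A question about home exercise that was prescribed makes sense in only one arm. If an interviewer puts it to intervention participants only, asking it identifies the arm. If it is put to everyone, the answer will usually do so.

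For outcomes obtained by interview, the interviewer is in effect the outcome assessor. Someone who knows the arm can, without intending to, prompt, probe or record answers differently in the two groups. Because participants and exercise staff know the allocation, assessor blinding is the main safeguard against observer bias at data collection. A procedure that discloses allocation during the outcome sessions weakens that safeguard for the outcomes that depend on the person asking.

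**Working it through.** The plan gives no figure on this point and no arithmetic applies. The check is to read the relevant rules together.

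1. **Who asks.** The Assessment section has an interviewer administer every questionnaire. The adherence measure under Programme adherence is called a questionnaire, so it falls under that rule.
2. **When.** It is collected at tests 2 and 3, the sessions at which the primary and secondary outcomes are also measured. Two of the three assessment sessions are affected. Baseline is not.
3. **What it reveals.** Home exercise is prescribed under Exercise programme and Table 1, which describe the intervention. Usual care describes a brochure and concomitant care. The subject of the question therefore separates the arms.
4. **Whether the interviewer is an assessor.** The SF-12, the Oxford scores and the HAPA scales are listed under Secondary outcomes and are questionnaires, so by step 1 they are obtained by interview. For these, the interviewer is an outcome assessor in the sense of the Randomisation section, whoever does the physical tests.
5. **Whether item order alone solves it.** Suppose the adherence items come last and the same interviewer returns. Test 2 outcomes are then already recorded and are protected. The interviewer, however, arrives at test 3, six months after surgery, knowing the arm. Asking last protects test 2 but not test 3.

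Exposure by outcome:

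| Outcome | How obtained | Exposure |
|---|---|---|
| Step count, sedentary time (primary) | Activity monitor: "Data from the device will be recorded and uploaded to a computer" | Largely spared |
| SF-12, Oxford scores, HAPA scales | Interviewer-administered questionnaire | Direct |
| Pain (visual analogue scale) | Mode not stated | Direct if elicited by interview |
| Timed Up and Go, blood pressure, waist circumference | Measured by an examiner | Only if the examiner is also the interviewer |
| Blood glucose, HbA1c, body fat percentage | Read from instruments | Little |

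Steps 1 to 4 give the conflict with the Randomisation section. The table gives its reach.

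**The case against.** The strongest reply is that nothing in the text makes the interviewer and the other assessors one person, and nothing fixes the order of items. A separate unblinded staff member could collect adherence without contradicting the rules quoted, and the blind would hold. The Assessment section also mentions a data collection training manual, which is not shown and may settle such details.

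This stands as far as it goes. A reader might infer that the plan obliges a blinded assessor to ask the question and so destroys the blind. The document does not support that: it permits the disclosure and states no safeguard, but it does not make disclosure certain. What remains is more than an omitted detail. A rule without exceptions and a named questionnaire sit against an explicit blinding claim, and those statements need to be reconciled. Reading self-report as self-completed would remove the problem, but it contradicts the interviewer rule.

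A second reply concerns impact. Pain, SF-12 and Oxford answers come from participants who know their arm, so reporting bias exists whatever the interviewer knows, and participants may disclose their arm unprompted. This is correct. The change removes a built-in route to disclosure and does not cure reporting bias. In addition, the statistician is kept blind through a separate allocation database, so assessor blinding is not the only protection in the trial.

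A reader might also infer that giving the control brochure at the baseline assessment point discloses allocation before baseline is complete. That does not follow. The Randomisation section places randomisation after all baseline measures, the phrase can simply denote the first time point, and no assessor is said to hand the brochure over.

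**Conclusion.** The point holds in limited form. As written, the Assessment and Programme adherence sections let the interviewer learn allocation at both follow-ups, contrary to the blinding claimed in the Abstract and under Randomisation.

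The main reach is the interviewer-elicited secondary outcomes. It extends to Timed Up and Go, blood pressure and waist circumference on the assumption, which the document neither states nor excludes, that one person does both jobs. It would be too much to say that every pain, function and clinical-marker comparison is compromised. Instrument-read markers leave little room for observer judgement, and the primary outcome is recorded by a device. How many assessors would in fact be unblinded, and how large any bias would be, cannot be worked out from the document.

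The conclusion rests on two readings: that the interviewer rule covers the adherence questionnaire, as its wording implies, and that controls have no prescribed home programme, as the description of usual care implies. The change is worth making because it is cheap and the secondary outcomes concerned are measured at both follow-ups.

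**What to change.** State an exception to the interviewer rule for the home-exercise adherence questionnaire. At tests 2 and 3, collect it as a self-completed form, sealed by the participant and handed in after all other measures. Offer a form of the same outward appearance to every participant, so that handing it out does not itself show the arm.

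Have the forms opened and entered by existing staff who do not assess outcomes. The data manager is one candidate, provided that role takes no part in assessment. Hold the adherence data apart from the blinded analysis database, because an adherence record that applies to one arm only would also disclose allocation to the statistician.

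The cost is one changed form and a fixed order at two sessions, with no added visit and no new staff. The small downside is that self-completion may leave slightly more missing adherence items than an interview would.

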### Data analysis

Differences in primary and secondary outcomes between groups will be compared using an intention-to-treat analysis. Once a participant is randomised to a study group, they will be considered a trial participant and analysed according to their allocated group, regardless of missing data for follow-ups or the amount of intervention received. Bivariate relationships will be tested with Pearson or Spearman correlations, independent *t*-tests or Mann–Whitney *U* tests (to examine relationships between the dependent variables and the independent variables) or chi squared tests for categorical variables. Each primary and secondary outcome will be analysed using a two-way repeated-measures analysis of covariance (ANCOVA) to determine differences between groups (exercise versus usual care) and between time points (test 1, test 2 and test 3). In addition, effects of the intervention targeting the psychological HAPA-based constructs on regular exercise is tested along with the key processes (mediation) involved. Data will be analysed with a linear mixed model with condition as between-participants effects and time points as within-participants effects. A path analysis will be used to determine mediation effects. Data analysis will be performed using statistical software STATA (STATA 13, Stata Corp, College Station, TX, USA) and Mplus. Statistical significance is set at *p* < 0.05 for all analyses.

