### Sample size

The sample size has been determined to be 50 patients in each group to detect an increase of 1200 (24%) daily steps (alpha 0.05, power 0.8) based on research indicating usual changes in step count after lower limb joint replacement [10]. The study that our sample size calculations are based upon experienced a low withdrawal rate of 4%. We have made a conservative estimate of a 10% withdrawal rate and, hence, will recruit 110 participants.

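### The repeated-measures ANCOVA counts the pre-randomisation baseline as an outcome time and names no post-baseline group contrast, so its group effect can dilute the treatment effect

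*Protocol article*

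**What the plan says.** The Data analysis section of the protocol article sets one model for all outcomes: "Each primary and secondary outcome will be analysed using a two-way repeated-measures analysis of covariance (ANCOVA) to determine differences between groups". The sentence goes on to name the two groups and the three time points, tests 1, 2 and 3. The Primary outcome measure section defines test 1 as the measurement at study entry, and the Randomisation section places allocation after baseline data collection. No group-by-time interaction, covariate or primary time point is named. The hypothesis at the end of the Background is that the programme raises daily steps at the time points after the intervention.

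The same section keeps every randomised participant in the allocated group, "regardless of missing data for follow-ups or the amount of intervention received". After a sentence on HAPA constructs and mediation, it adds: "Data will be analysed with a linear mixed model with condition as between-participants effects and time points as within-participants effects". Path analysis follows. The Secondary outcomes section lists the HAPA constructs among the secondary outcomes.

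The Sample size section reads "The sample size has been determined to be 50 patients in each group" and "to detect an increase of 1200 (24%) daily steps", with "alpha 0.05, power 0.8". No SD and no correlation between visits are given.

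**The concern.** Because test 1 precedes randomisation, its expected group difference is zero. A group effect averaged over three visits mixes that zero with the two follow-up differences. A time effect is not a treatment comparison. Neither of the two named differences therefore matches the hypothesis. If the group main effect is taken as the result, the trial reports a smaller effect than the one it was sized for, possibly with less power than planned.

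Two smaller matters arise in the same paragraph. Classical repeated-measures ANCOVA drops anyone with a missing visit, which would sit badly with the intention-to-treat statement, and test 3 exists only after surgery. For the HAPA constructs, two models are assigned with no rule for which result counts.

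**Working it through.** **Inputs.** Effect 1200 steps/day, 50 per arm, alpha 0.05 and power 0.8 come from the Sample size section. A two-sided test is assumed. The correlation ρ between visits is assumed to lie between 0.3 and 0.8, with compound symmetry.

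**The plan's own figure.** Without an SD, 50 per arm cannot be reproduced independently. Solving for the SD that gives power 0.80 for a two-sample t-test of 1200 steps with 50 per arm yields 2121 (2142 by the normal approximation). That SD is used below. Power is from the noncentral t distribution, with 98 degrees of freedom, or 97 with a baseline covariate.

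**Group main effect with test 1 as a level.**
- Estimate with equal effects at both follow-ups: (0 + 1200 + 1200)/3 = 800.
- If the effect is 1200 at test 2 and zero at test 3: (0 + 1200 + 0)/3 = 400.
- Variance of a participant's three-visit mean: SD²(1 + 2ρ)/3. The standard error of the group difference is the square root of that variance times 2/50.
- At ρ = 0.6: 2121 × √(2.2/3) × √(2/50) = 363, so 800/363 = 2.20 and power is 0.59.

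**Baseline-adjusted comparison at one follow-up.** Variance SD²(1 − ρ²). At ρ = 0.6: 2121 × 0.8 × √(2/50) = 339, so 1200/339 = 3.54 and power is 0.94.

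**Group-by-time contrast (mean of tests 2 and 3 minus test 1).** Variance SD²[(1 + ρ)/2 + 1 − 2ρ]. The estimate stays at 1200.

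**Baseline-adjusted comparison of the mean of tests 2 and 3.** Variance SD²[(1 + ρ)/2 − ρ²].

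Power with a true effect of 1200 at both follow-ups and 50 per arm with complete data:

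| ρ | Group main effect, three visits, no covariate | Follow-up mean minus baseline | Baseline-adjusted, one follow-up | Baseline-adjusted, follow-up mean |
|---|---|---|---|---|
| 0.3 | 0.72 | 0.78 | 0.84 | 0.96 |
| 0.5 | 0.63 | 0.90 | 0.90 | 0.98 |
| 0.6 | 0.59 | 0.95 | 0.94 | 0.99 |
| 0.7 | 0.55 | 0.99 | 0.98 | 0.997 |
| 0.8 | 0.52 | 0.999 | 0.997 | >0.999 |

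**Baseline as both covariate and outcome level.** Given the baseline value, the three-visit mean is two thirds of the follow-up mean plus a known term. Estimate and standard error both shrink by 2/3. The estimate is still 800, but power equals that in the last column.

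**The case against.** The strongest reply is that the dilution is one reading, and the least favourable. A two-way group-by-time model ordinarily contains the interaction, which keeps the full 1200 steps; at ρ = 0.6 the contrast above has power 0.95. The method is called an analysis of covariance, so baseline may well be the covariate, and then power is not lost. An article may leave covariates and missing-data methods to a fuller document. All of this stands. It makes the loss conditional, but it does not remove the fault: the text fixes three time levels and names group and time differences only, and neither answers the hypothesis.

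Three stronger readings are tempting, and the documents do not support them.
- A reader might infer a plain contradiction with intention to treat. The protocol never states a complete-case analysis. The conflict arises only if the ANCOVA is fitted in its classical form.
- A reader might infer that two models compete for the primary outcome. The mixed-model sentence stands between the HAPA sentence and the path analysis and may apply only there. The overlap is clear for the HAPA constructs and uncertain for step count.
- A reader might take the t-tests and Mann–Whitney tests as rival tests of treatment. The section assigns them to bivariate relationships.

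Nor is baseline as an outcome time wrong in itself. A constrained common baseline model keeps it there soundly, because it forces the group difference at test 1 to zero.

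**Conclusion.** The point holds in conditional form. As written, the model includes a pre-randomisation visit as an outcome level and does not name the contrast that tests the hypothesis.

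If the group main effect is tested and effects are equal at tests 2 and 3, the estimate is 800 instead of 1200, a loss of one third. If there is also no baseline covariate, power is about 0.72 to 0.52 against the planned 0.80. These power figures rest on an SD of 2121 back-solved from the plan, ρ of 0.3 to 0.8, compound symmetry, a two-sided test and complete data. It would go too far to say that the analysis will lose a third of the effect, since a group-by-time contrast would not.

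The missing-visit issue is a risk of the named method and is not a stated rule. The double assignment of models is established for the HAPA constructs only.

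**What to change.** For step count, sedentary time and the other outcomes, use the linear mixed model already named. Take tests 2 and 3 as outcomes, with the baseline value as covariate (or a constrained common baseline), and include group, time and group-by-time. Use all available visits, which also fits the intention-to-treat statement.

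State the post-baseline group contrast or contrasts that test the Background hypothesis. That hypothesis covers all times after the intervention, so it does not by itself make test 2 the sole primary time; if one time is to be primary, the investigators need to say so. State that this one model also governs the HAPA constructs, and keep path analysis for mediation.

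The cost is a rewording of the Data analysis section. No further participants, visits or data are needed, since baseline is already collected and Stata, which the protocol names, fits such models. The Trial status section says that the trial is ongoing, so the change is best recorded before unblinding.
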